### Randomisation

Randomization will be done with each session in an out-patient clinic as a cluster unit. Currently there are 10 sessions per week per study site. Before the study, we will randomly draw the sessions by computer generated random sequence (block randomization with each hospital as a block unit), so that 5 sessions will be treated as intervention group and another 5 sessions will be treated as control group per week. Participants who consent to participate in the study will be assigned to either intervention or control group depending on the out-patient clinic session that they are seeking consultation. By using this experimental design, we can ensure similar proportion of smoking cancer patients will fall into the intervention and control group in each out-patient clinic, and each out-patient clinic will have a similar proportion of cancer patients into the intervention/ control group. We expect the intervention and control group would have similar socio-demographic profile, smoking history, and clinical history and we shall check for any differences, and if any, we shall adjust for them in the analyses. In using the cluster randomization design with a session being a cluster unit, the patients who are randomized into the experimental and control groups would have less chance to meet each other in the out-patient clinic and discuss the contents of the smoking cessation interventions.

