### Analysis

Data analysis was performed using the Statistical Package for Social Science software, version 20.0 for Windows. When assessing the effectiveness of interventions between the two groups, we will first compare the baseline characteristics of the patients using chi-square test for categorical variables and *t*-test or Wilcoxon rank-sum test for continuous variables between the experimental and control groups. The primary analysis will be an unadjusted intention-to-treat analysis of the difference in self-reported 7-day point prevalence quit rate of the smoking cancer patients during 6-month follow up between the two groups. The analysis will be performed using Pearson’s chi-square test or with the use of Fisher’s exact test, if there were five or fewer participants per cell. Similar approach will be used to estimate the differences in secondary outcomes (e.g. self-reported 7-day PP quit rate at 12-month follow-up and the biochemically validated quit rate at 6-month follow-up, percentage of patients reduced smoking by at least 50 % at 6- and 12-month follow-up compared to baseline, and quality of life at 6 and 12 months) between groups. Crude odds ratios (ORs) for quitting will be estimated using logistic regression model and were compared with ORs that were adjusted for baseline variables (e.g. sex, age, education, stage of readiness). Those who are lost to follow-up or refuse to participate in the validation tests, will be treated as smokers with no reduction in cigarette consumption compared with (a) baseline, as the main analysis (by intention to treat), (b) the most recent level and (c) complete case (per protocol) analysis by excluding subjects with missing data as a sensitivity analysis.

For the process evaluation, all qualitative data from interviews will be tape-recorded and transcribed verbatim. Content analysis will be employed and themes identified. The constant comparative method will be used to search for common constructs and themes about the implementation and the effect of the intervention as perceived by the participating subjects.

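### Blocking on hospital balances sessions rather than patients, so within-hospital balance is expected but not ensured, and the primary test leaves out the blocking factor

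*Protocol article*

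**What the plan says.** The Randomisation section of the protocol article makes the clinic session the unit: "Randomization will be done with each session in an out-patient clinic as a cluster unit". On numbers it says "Currently there are 10 sessions per week per study site". The draw is made before the study as "block randomization with each hospital as a block unit". The resulting weekly split at a site is then given in these terms: "so that 5 sessions will be treated as intervention group and another 5 sessions will be treated as control group per week". A patient's arm is not drawn individually; it follows from the session attended ("depending on the out-patient clinic session that they are seeking consultation"). From this the section concludes that "we can ensure similar proportion of smoking cancer patients will fall into the intervention and control group in each out-patient clinic". For imbalance in socio-demographic profile, smoking history or clinical history it promises "we shall check for any differences, and if any, we shall adjust for them in the analyses". Hospital is not among those domains.

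The Analysis section fixes the main comparison: "The primary analysis will be an unadjusted intention-to-treat analysis of the difference in self-reported 7-day point prevalence quit rate". The test is Pearson's chi-square, or Fisher's exact test for small cells, between the two groups as a whole. Neither hospital nor session enters it. Crude odds ratios are then set beside odds ratios adjusted for baseline variables; sex, age, education and stage of readiness are given as examples.

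**The concern.** A 5:5 split of sessions gives a 50:50 split of patients only on average. Nothing in the design controls how many eligible smokers attend and consent in each session, so the arm split can drift from hospital to hospital. If hospitals also differ in their underlying quit rates, each realised trial carries some hospital difference inside the crude arm difference. A pooled test that ignores hospital does not count this extra variation, so its error rate can rise above 5 % and its estimate is somewhat noisier than it need be. Leaving out the factor on which the randomisation was blocked is a stated choice here, because the primary analysis is fixed as unadjusted.

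**Working it through.** **1. The plan's own figures.** For 29 % against 18 %, two-sided 5 %, power 0.80, mean rate 0.235:

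n = [1.960·√(2×0.235×0.765) + 0.842·√(0.29×0.71 + 0.18×0.82)]² / 0.11² = 232.05, so 233 per group, as the Power calculation section states. Then 233/0.85 = 274.1, and with 233/20 = 11.65 patients per cluster, 274 × [1 + (11.65 − 1)×0.002] = 279.8, so 280. All three figures reproduce. The article gives no figure for patient balance within hospital.

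**2. Inputs for the balance check.** From the article: 5 hospitals, 10 sessions each, 5:5 per hospital, 560 patients, control quit rate 18 %. Assumed, because the article is silent: hospitals of equal size (560/5 = 112 patients); coefficient of variation (CV) of session size 0, 0.4 or 0.8; five equally spaced hospital quit rates, 14-22 % or 8-28 %; sessions drawn once; no session correlation unless stated.

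**3. A hospital's share of patients in the intervention arm.** The mean is 50 %. Its variance is roughly the binomial part, 0.25/112, plus the part from choosing 5 of 10 unequal sessions, 2.5·CV²/100 = 0.025·CV².

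| CV | SD by formula (points) | SD simulated | 95 % range | Chance that some hospital is outside 40:60 |
|---|---|---|---|---|
| 0 | 4.7 | 4.7 | 41-59 % | about 0.15 |
| 0.4 | 7.9 | 7.8 | 35-65 % | about 0.67 |
| 0.8 | 13.5 | 13.1 | 25-75 % | about 0.95 |

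If sessions were redrawn every week for the 78 weeks of recruitment, the SD would be 4.7-5.0 points whatever the CV.

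**4. What reaches the crude difference.** With 280 per arm, hospital h contributes (112/280)·(2s − 1)·p = 0.8·(s − 0.5)·p, where s is its intervention share and p its quit rate. Since s averages 0.5, the contribution averages zero; the simulated mean was 0.0 points in every setting. Its SD is 0.8 × SD(s) × √Σ(p − 18 %)². The root is √40 = 6.3 points for 14-22 % and √250 = 15.8 points for 8-28 %.

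- 14-22 %: 0.8×0.047×6.3 = 0.24 points (CV 0) to 0.8×0.131×6.3 = 0.66 (CV 0.8; simulated 0.68).
- 8-28 %: 0.8×0.047×15.8 = 0.6 points (CV 0) to 0.8×0.131×15.8 = 1.66 (CV 0.8; simulated 1.69).

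The sampling standard error is √(2×0.18×0.82/280) = 3.25 points, and the planned effect is 11 points. As a single example, a 60:40 split in a 28 % hospital with 40:60 in an 8 % hospital shifts the crude difference by 0.8×(0.1×10 + 0.1×10) = 1.6 points.

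**5. Type I error.** For 8-28 % and CV 0.8, the within-hospital variance averages 0.1476 − 0.0050 = 0.1426, giving a standard error of √(2×0.1426/280) = 3.19 points. The true SD of the crude difference is √(3.19² + 1.69²) = 3.61, which is also the simulated value. The crude test uses about 3.25, so its cut-off is really 1.96×3.25/3.61 = 1.76 SDs, a two-sided error of about 7.8 %. Simulation gave 7.5 %, against 4.8 % for a Cochran-Mantel-Haenszel (CMH) test by hospital. In the other equal-size settings the crude test gave 4.5-5.8 % and CMH 4.7-5.2 %. A run with hospitals of unequal size at CV 0.4 gave 6.2 % and 5.4 %.

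A separate simulation let hospital rates vary on the logit scale, with session-size CV 0.5 to 0.9:

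| SD of hospital logits | Pooled test | Stratified test |
|---|---|---|
| 0.3 | 5.2-5.7 % | not reported |
| 0.5 (about 12-27 % at ±1 SD) | 5.9-8.5 % | 4.8-4.9 % |
| 0.8 | 7.2-12.4 % | about 5 % |

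**6. Estimate and power under a true 11-point effect** (rates 8-28 %, no attrition). Mean estimate, crude against stratified: 10.97 and 10.98 (CV 0.4); 10.96 and 10.96 (CV 0.8). Power: 85.7 % and 86.8 %; 83.6 % and 84.9 %.

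**7. What hospital stratification does not do.** With session correlation added (CV 0.4, 8-28 %), type I error for crude and CMH is 5.6 % and 5.0 % at the plan's 0.002, 8.7 % and 7.7 % at 0.02, and 12.7 % and 11.9 % at 0.05.

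**The case against.** - **Blocking already does most of the work.** At CV 0.4 and rates of 8-28 %, drawing sessions without hospital blocks gives a hospital-mix SD of 2.24 points and a crude error rate of 9.9 %; with blocks these are 1.0 point and 5.8 %. This stands. A reader might infer that the promised balance fails. The document does not support that: the expected share is 50 % in every hospital, and only the guarantee is missing.
- **There is no bias.** A reader might infer that the crude estimate is confounded by hospital. Under a random 5:5 draw it is not; the mean contribution is zero. A systematic error would need recruitment that differs by arm, and differs in that way between hospitals. Patients do consent after sessions are allocated, so this is possible, but nothing in the article shows it.
- **The size rests on assumptions.** The article gives neither session-size nor between-hospital variation. With 4,000 replicates the Monte Carlo error near 5 % is √(0.05×0.95/4000) = 0.34 points, so 5.2 % cannot be told from nominal. This stands.
- **The draw may be weekly.** The article does not say whether one weekly pattern is kept. If each week is drawn afresh, the excess imbalance nearly vanishes. A single draw fits the 20 clusters in the power calculation better than 50 × 78 = 3,900 session occasions would, but doubt remains.
- **The covariate list is open.** It is given as examples, so the absence of hospital from it is not itself an error. Only the unadjusted primary test is fixed.

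**Conclusion.** The concern holds in a limited form. The article promises more balance than a 5:5 draw of sessions can guarantee, and it fixes a primary test that leaves out the blocking factor. The consequence is extra chance variation and not bias: an SD of about 0.2-1.7 points against a sampling error of about 3.3. Type I error is about 5-6 % in most settings. It reaches about 7.5-8.5 % only when session sizes and hospital quit rates both vary widely, and goes higher only under more extreme hospital variation. These figures assume sessions drawn once and no session correlation. A reader might also take hospital stratification as the answer to the whole weakness of the crude test. It is not: at a session correlation of 0.02 or more, ignoring sessions matters more, and stratifying by hospital barely helps. Priority is minor to moderate.

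**What to change.** - **Randomisation section:** replace 'can ensure' with 'expect', and state that sessions are what is balanced within each hospital. Stating whether the session pattern is drawn once or each week would settle how much imbalance to expect.
- **Analysis section:** make hospital a stratum (for example a Mantel-Haenszel risk difference) or a fixed effect in the primary comparison, within an analysis that also accounts for session clustering. Include hospital in the adjusted models.
- **Reporting:** tabulate patients by arm within hospital.

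The cost is a few sentences of plan text; no patients or procedures are added. The downside is about 1-3 points of power if hospitals do not differ at all.

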### Primary and secondary outcomes

The primary outcome is the self-reported 7-day point prevalence (PP) quit rate of the smoking cancer patients during 6-month follow up. The secondary outcomes include (a) self-reported 7-day PP quit rate at 12-month follow-up and the biochemically validated quit rate at 6-month follow-up (non-smoking status is confirmed by a carbon monoxide level in expired air < 9 ppm and saliva cotinine level < 115 ng/mL in parallel test), (b) percentage of patients reduced smoking by at least 50 % at 6- and 12-month follow-up compared to baseline, (c) percentage of patients with quit attempt(s) at 6- and 12-month follow-up, (d) change in the intention to quit smoking (stage of readiness to quit) at 6- and 12-month follow-up compared to baseline, (e) change in risk perceptions of continued smoking at 6- and 12-month follow-up compared to baseline, and (f) change in health-related quality of life at 6- and 12-month compared to baseline.

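### Data-driven covariate adjustment promised under Randomisation is not reconciled with the unadjusted primary test, which leaves out hospital and prognostic baseline variables already collected

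*Protocol article*

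**What the plan says.** Two sections of the protocol article bear on covariate adjustment.

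- **Randomisation.** Clinic sessions are randomised, with each hospital as a block. The authors expect similar arms and add: "we shall check for any differences, and if any, we shall adjust for them in the analyses". The sentence names no covariates, gives no criterion for a difference, and does not say which analyses it covers.
- **Analysis.** The first step is a set of between-arm tests: "we will first compare the baseline characteristics of the patients using chi-square test for categorical variables", with a t-test or Wilcoxon test for continuous variables. Then: "The primary analysis will be an unadjusted intention-to-treat analysis". The method is given as "The analysis will be performed using Pearson’s chi-square test or with the use of Fisher’s exact test". Crude odds ratios from logistic regression are to be set beside odds ratios "adjusted for baseline variables (e.g. sex, age, education, stage of readiness", a list given only as examples. This adjusted analysis does not depend on the baseline tests and is not called primary.

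The Analysis section does not mention the conditional rule, and the Randomisation section does not mention the unadjusted primary test. Neither names hospital as a covariate.

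**The concern.** A rule to adjust for whatever turns out to differ has two weaknesses. It lets the observed baseline data choose the model. It also chooses on the wrong ground: a covariate earns its place by predicting the outcome, and under sound randomisation a significant baseline difference is a chance event that says nothing about prediction. The Analysis section's tests also treat patients as independent although sessions are randomised, so any within-session correlation would make chance flags more frequent.

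If a difference appears, no sentence says whether the rule touches the primary comparison. Meanwhile the primary test makes no use of the randomisation block, or of likely predictors of quitting that the trial collects anyway: stage of readiness, smoking history, self-efficacy and age. At stake are the clarity of which result decides the trial, and precision that could be had at almost no cost.

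**Working it through.** **1. Is the primary analysis defined more than once?** The Primary and secondary outcomes section names one outcome: "The primary outcome is the self-reported 7-day point prevalence (PP) quit rate of the smoking cancer patients during 6-month follow up". The Analysis section names one primary analysis of it and labels it unadjusted. The sample size can be checked against that label.

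Inputs from Power calculation: 29% against 18%, 5% level (taken as two-sided), power 0.80.

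- Pooled rate = (0.29 + 0.18)/2 = 0.235
- Null term: 1.96 × √(2 × 0.235 × 0.765) = 1.1753
- Alternative SD: √(0.29 × 0.71 + 0.18 × 0.82) = 0.5946; times 0.8416 = 0.5004
- n = (1.1753 + 0.5004)² / 0.11² = 232.1, rounded up to **233 per arm**, the stated figure

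So the sample size rests on an unadjusted comparison of two proportions, in line with the Analysis section. (It is the uncorrected chi-square figure, although the text cites Fisher's exact test; that is a separate matter.)

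**2. How readily would the conditional rule fire?** The documents give neither a number of covariates nor a threshold. Assuming K independent covariates each tested at 5%, with sound randomisation, the chance of at least one flag is 1 − 0.95^K:

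| K (assumed) | Chance of at least one flag |
|---|---|
| 4 | 19% |
| 10 | 40% |
| 20 | 64% |

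The Structured questionnaire section lists many baseline items, so a trigger is quite likely.

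**3. What does the rule cost in type I error?** Null simulation, all settings assumed: 280 per arm, 18% quit rate at the covariate mean, 10 or 20 covariates of which four have an odds ratio of 1.0, 1.5 or 2.0 per SD, no clustering, 4,000 runs per setting.

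| Rule | Type I error across settings |
|---|---|
| Unadjusted | 4.6% to 6.0% |
| Adjust only for flagged covariates | 4.3% to 5.9% |
| Claim whichever is significant | 5.1% to 6.2% |

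Within settings, free choice added about 0.2 to 0.6 percentage points over the unadjusted test.

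**4. What could prespecified adjustment gain?** If fixed covariates explain a share R² of outcome variance (assumed), the effective size is about 233/(1 − R²), and power = Φ[(0.11 × √n − 1.1753)/0.5946].

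| R² (assumed) | Effective n per arm | z | Power |
|---|---|---|---|
| 0 | 233 | 0.85 | 80% |
| 10% | 233/0.9 = 259 | 1.00 | 84% |
| 20% | 233/0.8 = 291 | 1.18 | 88% |

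These start from 233 evaluable patients per arm and ignore clustering, so they show the order of the gain and do not forecast the trial's power.

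**The case against.** The strongest reply is that the plan already reads coherently: an unadjusted primary test, with adjusted odds ratios in support. The specific, labelled statement in the Analysis section governs a general remark made under Randomisation, and that remark can be read as pointing to the adjusted odds ratios. An unadjusted primary test is a legitimate choice. The article is condensed, and a closed covariate list is something an analysis plan may hold. The power gain measures the benefit of a preferred model, not harm from the present wording.

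Most of this stands. A reader might infer that the primary result has two definitions, one chosen after looking at the data. The documents do not support that: the Randomisation section never calls its adjustment primary or says that it replaces the chi-square test, and the sample size fits the unadjusted test. A reader might also infer that prognostic variables enter only if imbalanced. That fails too, because adjusted odds ratios are planned regardless, with stage of readiness among the examples. And since that list is open, it cannot be said that hospital is excluded from the adjusted model.

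What remains does not rest on omission. The conditional rule is in the text, it depends on the data, and nothing confines it to supportive analyses. A test labelled unadjusted leaves out hospital and predictors by definition.

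On the other side, the simulation assumed sound individual allocation. Here sessions are drawn before the study, patients are approached afterwards, and staff know which sessions are control, so selective recruitment is possible. As an illustration (assumed: quit rates of 30% if ready and 15% if not, about half ready, 280 per arm, no true effect), a 10-point imbalance in readiness shifts the difference by 0.10 × 15 = 1.5 points. With SE √(2 × 0.225 × 0.775/280) = 3.5 points, two-sided type I error becomes about 7%; a 20-point imbalance gives about 14%. The documents do not show that such imbalance will arise. The example only shows why covariates are better fixed beforehand than after a look at baseline.

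**Conclusion.** The point holds as a matter of prespecification and efficiency, not as a contradiction over what is primary. The Randomisation section adds an open-ended rule, driven by chance imbalance, that the Analysis section neither repeats nor limits, and the primary test forgoes the block factor and collected predictors. The type I error cost of the wording is small under sound randomisation: about 0.2 to 0.6 percentage points under the simulated settings, without clustering. The possible gain from fixed adjustment is moderate: power of about 84% at R² = 10% or 88% at R² = 20%, against 80%. Both R² values are assumptions; the documents give no figure for how well these variables predict quitting. The change is worth making because it costs almost nothing, not because the present plan is invalid.

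**What to change.** 1. Delete the conditional adjustment clause under Randomisation and the baseline significance tests under Analysis. Describe baseline balance without p-values.
2. Prespecify one deciding analysis. Preferably, adjust it for hospital and a short fixed list of collected predictors, for example stage of readiness, baseline cigarettes per day and age, with session as cluster. Report a standardised risk difference and an odds ratio, with the unadjusted result as supportive.
3. If the unadjusted test is kept as primary, which is acceptable, state that it decides the trial whatever the baseline comparison shows, and fix the covariates of the adjusted odds ratio in advance, including hospital.

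Cost: the third option changes wording only. The preferred option also changes the primary model, so it must be settled before outcome data are seen. Neither needs new data, since the covariates come from the baseline questionnaire or medical records and hospital is known. A rule for missing baseline values is the only further work.

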### Intervention

#### Control group

Subjects in the control group will receive usual care provided at the site, a generic self-help smoking cessation booklet published by the Hong Kong Council on Smoking and Health, a brief face-to-face counselling at baseline plus telephone follow ups by nurses to show support and care on their disease condition.

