**Methods:**

A cluster randomized controlled trial will be employed. Cancer patients who continued smoking after the diagnosis of cancer and have medical follow-up at the out-patient clinics of the five acute hospitals in Hong Kong will be invited to participate. Subjects in the experimental group will receive (1) health warnings of smoking based on a special designed leaflet; and (2) a patient-centred counseling from nurse counselors with emphasis on risk perceptions of smoking to cancer prognosis. Additionally, they will receive two more telephone counseling at 1-week and 1-month. Control group receive standard care and a generic self-help smoking cessation booklet. Outcomes measure include (a) self-reported and the biochemically validated quit rate, (b) patient’s smoking reduction by at least 50 % compared to baseline, (c) quit attempt(s), (d) change in the intention to quit, (e) change in risk perceptions of smoking, and (f) change in health related quality of life.

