### Procedure

Approval for the study has been obtained from five hospital ethics committees (Kowloon West Cluster Research Committee; Hong Kong East Cluster Ethics Committee; Kowloon Central/Kowloon East Research Ethics Committee; Hong Kong West Cluster Ethics Committee; and New Territories West Cluster Clinical & Research Ethics Committee). To ensure the rights of all participants will be protected, the research carried out will be in compliance with the Helsinki Declaration (http://www.wma.net/en/30publications/10policies/b3/index.html). Research assistants will approach patients in the oncology out-patient clinic and ask them whether they are smokers or not. The eligible subjects will then invite to participate in this study after they are told the purpose of the study. They will be given the option of participating or refusing involvement in the study and will be told that their participation is voluntary without prejudice. Written consent will then obtain from all participants.

To evaluate the effectiveness of a smoking cessation intervention using risk communication approach, a total of 560 eligible Chinese cancer patients were recruited from five out-patient clinics in Hong Kong. After completing the baseline questionnaire, subjects will receive proposed intervention according to their group assignment. Four consecutive (3-, 6-, 9- and 12-month) follow ups will be conducted by trained interviewers (blinded to the group assignment) with all subjects via telephone. We will assess hospital readmission and other clinical outcomes from the participants’ medical records accordingly. Patients who have successfully quit smoking at 6-month will be invited to come back to the out-patient clinic and have biochemical validation tests (saliva cotinine test and exhaled CO test). We will offer HKD300 (USD38.5) per client to cover their travel expenses and time cost. From our previous experience, such an incentive is necessary to secure a sufficiently high response rate.

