#### Training and quality assurance of the nurse counsellors and research assistants

All the research nurses are qualified smoking cessation counsellors, and they will be provided with specific training workshop by the principal and co-investigators prior to the commencement of the study. They will be equipped with the necessary knowledge and skills to deliver both the smoking cessation counselling using the motivational interviewing techniques and stages of change model. Regular case conference, quality checks through audio-taping, and audit procedures will be conducted to ensure and maintain the quality and uniformity of the counselling interventions. The research assistants will be trained by the principal and co-investigators to screen eligible case, conduct baseline and follow-up surveys and procedures of biochemical validations (saliva cotinine test and exhale CO test). Briefing sessions will also be provided to oncologists and oncology nurses in using the special designed leaflets.

Since the same batch of oncologists and oncology nurses working in the setting would contact cancer patients in both the intervention and control group, a quality assurance mechanism will be used to prevent the contamination of intervention and control group: (1) a clear instruction and reminder will be given to the participating doctors and nurses before the start of the RCT study, and we will explain the principle of RCT and reinforce them the different treatments for the experimental and control groups; (2) a specific risk communication leaflet will be attached in front of the patients’ medical records in the intervention sessions, and doctors and nurses will fill up a checklist to make sure if they have delivered the intervention at the end of each consultation; (3) patients in the experimental group will be invited to complete a satisfaction survey during telephone follow-up to see if they have received the risk communication messages from physicians and nurses during baseline intervention; and (4) doctors and nurses will be reminded that they need not deliver the intervention during the “control” clinic sessions and only usual care will be given.

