### Power calculation

Sample size is calculated by “Power Analysis and Sample Size (PASS) v. 13” (http://www.ncss.com/pass.html) and based on the main outcome variable according to the main hypothesis, the 7-day point prevalence self-reported quit rate at 6-month in the experimental group is higher than the control group. A previous RCT study [28] conducted in Australia, which applied motivational intervention to 137 smoking patients with mixed cancer sites. Based on that study, the self-reported 7-day point prevalence quit rate at 6-month follow up was 29 % for the intervention group and 18 % for the control group. To detect a statistical difference at 5 % significant level and a power of 0.8, 233 patients will be needed in each of the 2 groups (based on independent samples Fisher exact test). With reference to the local RCT on smoking cessation intervention for cardiac patients [22], we assume a 15 % attrition rate at the 6-month, and 274 patients will be required in each group to achieve a significant outcome. Accounting for the clustered randomized sampling design with 20 clusters (sessions) and an intra-class correlation of 0.002, 280 patients will be required per group, adding up the total sample size to 560 from the experimental and control groups together.

From the information provided by our clinical partners on site screening, there are around 2000 new patients per hospital per year. According to our previous qualitative study [23] conducted in an out-patient clinic on Chinese current smokers and ex-smokers, about 13.7 % patients continued smoking after receiving a cancer diagnosis (274: 13.7 % of 2,000). However, more than 50 % of these smokers were reluctant to quit (137: 50 % of 274). In a rough estimation, there will be around 700 eligible subjects in five acute Hospital Authority hospitals each year. We have confidence that we can recruit adequate subjects (560) according to the power analysis within an 18-month (78-week) recruitment period.

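### The patient survey listed as a contamination safeguard goes only to the experimental group, so it cannot detect leakage to controls and may reveal allocation to blinded interviewers

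*Protocol article*

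**What the plan says.** The section on training and quality assurance explains that the same oncologists and oncology nurses see patients of both groups, and states that "a quality assurance mechanism will be used to prevent the contamination of intervention and control group". It then lists four steps:

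1. Instruct the participating doctors and nurses before the trial starts.
2. Attach the leaflet to records in intervention sessions, and have staff complete a delivery checklist.
3. Survey patients about receipt of the risk messages: "patients in the experimental group will be invited to complete a satisfaction survey during telephone follow-up".
4. Remind doctors and nurses that they need not deliver the intervention in control "clinic sessions and only usual care will be given".

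Under Control group, controls receive usual care, a generic booklet and "a brief face-to-face counselling at baseline plus telephone follow ups by nurses to show support and care on their disease condition". The article does not say which nurses give this contact. The same training section says of the study's own nurses: "All the research nurses are qualified smoking cessation counsellors".

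Under Procedure, the telephone follow-ups at 3, 6, 9 and 12 months cover all subjects and will be "conducted by trained interviewers (blinded to the group assignment". Under Primary and secondary outcomes, the primary outcome is self-reported 7-day point prevalence quitting at 6 months. Change in risk perceptions at 6 and 12 months is secondary outcome (e).

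**The concern.** The article treats contamination as a threat that needs active control. Contamination means that controls hear the risk messages, so it can be seen only in controls. The one step that asks patients about receipt leaves controls out. A high receipt rate in the experimental group would show that the intervention was delivered, and would say nothing about the other group.

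Controls also have a plausible route of exposure. They meet a nurse face to face at baseline and are then telephoned by nurses, which are the channels that carry the experimental counselling. Any leakage would raise the control quit rate and shrink the primary difference.

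There is a second effect. The survey is placed within telephone follow-up. If the blinded interviewers give it, asking one group only shows them the allocation of each patient they ask. They are also the people who record a self-reported primary outcome.

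**Working it through.** **Each step against what it could show about controls**

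| Step | Addressed to | Shows exposure among controls? |
|---|---|---|
| 1. Instruction | Doctors and nurses | No; preventive only |
| 2. Leaflet and checklist | Intervention sessions | No; records delivery |
| 3. Receipt survey | Experimental patients | No; controls not asked |
| 4. Reminder | Doctors and nurses in control sessions | No; preventive only |

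None of the four names the control counselling or calls, and none collects receipt data from controls. The audio-taping and audit in the same section are described as serving the quality and uniformity of counselling. They are not among the four steps.

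**Blinding.** Three statements have to be combined: the survey takes place during telephone follow-up, only experimental patients get it, and follow-up interviewers are blinded. If the same interviewers do both, the three do not fit together. The article does not say who gives the survey, so this part is conditional.

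**What leakage would cost, if it happened.** Inputs from Power calculation: quit rates of 29 % and 18 %, 5 % significance (sidedness not stated, taken as two-sided), power 0.8, and "233 patients will be needed in each of the 2 groups". The leakage share c is not in the document and is assumed.

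Formula (pooled-variance normal approximation, with p̄ the mean of the two rates and d their difference):

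n = [1.96·√(2p̄(1−p̄)) + 0.8416·√(p₁(1−p₁) + p₂(1−p₂))]² / d²

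Plan's own case: p̄ = 0.235, d = 0.11. The terms are 1.96 × √0.35955 = 1.175 and 0.8416 × √0.3535 = 0.500. So n = (1.676)² / 0.0121 ≈ 232.1, rounded up to 233. This reproduces the stated figure, and power at 233 is 0.802.

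With leakage at full effect, the control rate is 18 % + 11c points and the experimental rate stays at 29 %:

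| Assumed c | Control rate | Difference | Power at 233 per group | n per group for 80 % |
|---|---|---|---|---|
| 0 | 18.0 % | 11.0 | 0.802 | 233 |
| 0.1 | 19.1 % | 9.9 | 0.707 | 292 |
| 0.2 | 20.2 % | 8.8 | 0.597 | 375 |
| 0.3 | 21.3 % | 7.7 | 0.482 | 498 |

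Exact enumeration of the chi-square test at 233 per group gives 0.805, 0.710, 0.600 and 0.484. If leaked content were worth half the effect, c = 0.2 would give 18 % + 0.2 × 5.5 = 19.1 %, which is the c = 0.1 row: power 0.707.

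**The case against.** A reader might infer more than the article supports, and the other side is right on several counts.

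- **That the control contact contradicts the fourth step.** The reminder is addressed to clinic doctors and nurses. If study nurses give the control contact, the two passages fit together. The conflict arises only if clinic nurses give it, which the article does not say. The telephone calls also fall outside clinic sessions.
- **That the control contact carries quitting advice.** Its stated purpose is support for the disease condition, and that phrase most naturally covers both the counselling and the calls. It reads as an attention control. Nothing in the article shows that leakage will occur.
- **That a null result could not be told apart from leakage.** Change in risk perceptions is measured in both groups. Leakage strong enough to alter quitting should raise it among controls. The check is indirect, but controls are not unobserved.
- **That the power loss is a finding about this trial.** The leakage shares are assumed, and each exposed control is credited with the effect of a whole package: warning, leaflet, counselling and two calls. The bias also runs towards no difference, so it would not create a false positive.
- **That the abstract misdescribes the control group.** It says "Control group receive standard care and a generic self-help smoking cessation booklet". Omitting the nurse contact there is ordinary condensation. Which nurses give the contact, and from what script, is detail that a journal article commonly leaves to the full protocol. Sessions are also randomised partly to keep patients of the two groups apart.

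None of this answers the point about the third step. The article states the survey, gives its purpose and restricts it to the group in which that purpose cannot be met.

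**Conclusion.** The point holds for the receipt survey. As specified it checks delivery and cannot detect leakage to controls. Whether it also unblinds interviewers depends on who gives it. The other stated check on controls is the indirect one through risk perceptions.

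The size is unknown, because the article gives no leakage rate. The power figures (71 %, 60 % and 48 % under 10 %, 20 % and 30 % leakage at full effect) show why receipt among controls is worth measuring. They do not predict what will happen. This is a cheap improvement worth making, not a flaw that invalidates the design.

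**What to change.** Put the same message-receipt items to both groups, after the smoking items of the 6-month call. Word them around the specific risk messages (smoking's effect on cancer treatment and prognosis), so that having the generic booklet does not count as receipt. Report receipt by group, beside the between-group change in risk perceptions. Asking everyone also removes the signal of allocation to the interviewer.

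Reword the fourth step so that control patients receive usual care plus the contact described under Control group. That settles the apparent mismatch whichever nurses give it.

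The cost is a few extra questions to about 280 controls who are already telephoned. Sample size and primary analysis do not change. The items could slightly prime controls before the 12-month secondary outcomes; asked last at 6 months, they cannot affect the primary outcome. Using separate nurses for controls, a control script and audio checks of control contacts are optional operational choices. Separate nurses would have their own drawback, since counsellor would then be confounded with group.
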